### **Objectives**

Primary Objective:

- To assess the time from randomization until an improvement (within 84 days) defined as two points on a seven point ordinal scale or live discharge from the hospital in high-risk patients (group 1 to group 4) with a SARS-CoV-2 infection requiring hospital admission by infusion of plasma from subjects after convalescence of a SARS-CoV-2 infection or standard of care.

Secondary Objectives

1. To assess overall survival, and the overall survival rate at 28, 56 and 84 days.
2. To assess SARS-CoV-2 viral clearance and load, cytokine changes over time as well as antiviral antibody titres.
3. To assess percentage of patients that required mechanical ventilation
4. To assess time from randomization until discharge

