### **2.2 Secondary Objectives**

- To assess overall survival, and the overall survival rate at 28, 56 and 84 days.
- To assess SARS-CoV-2 viral clearance and load as well as antibody titres.
- To assess percentage of patients that required mechanical ventilation.

- To assess time from randomization until discharge

For detailed endpoints see sections 10.3.2. and 10.3.3

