### **7.3.3 Laboratory parameters**

Nose/throat swabs are collected at day 0 and day 1 (before first CP administration) and subsequently at day 2, 3, 5, 7, 10, 14, 28 or until discharge. Serum for SARS-Cov-2 diagnostic is collected at baseline and subsequently at day 3, 7, 14 and once during the follow-up period (between day 35 and day 84). Serum collection on the following days is optional: day 1, 2, 3, 10 and 28. Details on sample collection and schedule will be provided in the laboratory manual.

Nasopharyngeal swabs are analysed for SARS-CoV-2 RNA viral load by semi-quantitative real-time RT-PCR in the laboratory of Prof. [name] (Center for Infectious diseases, University Hospital Heidelberg). Patient serum obtained at the different time points is stored

at -20° C until further use. Antibodies directed against SARS-CoV-2 are going to be analysed in recipient serum before (day1) and after (day 3) treatment. IgG Antibodies are detected in standard ELISA tests. Further, analyses for neutralizing antibodies are performed by [name]. [name] (DKFZ, Heidelberg). Cytokine analyses is performed in the laboratory of PD [name] (NCT Heidelberg) with the Bio-Plex Pro Human Cytokine 48-Plex Screening Panel (Biorad, Munich, Germany). To evaluate the effects of CP onto inflammation and cytokine levels, a first analysis is performed after the first randomized 40 patients. All other serum specimens are analyzed at the end of trial.

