# **10 Statistical Considerations**

## **10.1 Study Design**

This is a randomized open-label, multicenter phase-II study in patients with severe SARS-CoV-2 disease subjects

*Randomisation (rf. also to chapter 6.8):*

Randomisation is done either into experimental arm E or into standard arm S in a 1:1 ratio using block randomisation stratified for the factor "patient group", defined by group 1 (patients with hematological malignancies, history of stem cell transplantation and/or active cancer therapy – incl. chemotherapy, radiotherapy, surgery – within the last 24 months or less.), group 2 (drug induced immunosuppression not meeting the criteria of group 1), group 3 (age  $\geq 50$  - 75 years and meeting neither the criteria of group 1 nor group 2 and Lymphopenia  $< 0.8 \times G/I$  and/or D-dimer  $> 1\mu g/mL$  and group 4 (age  $> 75$  years and meeting neither the criteria of group 1 nor group 2).

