### 10.3.2 Secondary Endpoints

Overall survival, defined as the time from randomization until death from any cause

28-day, 56-day and 84-day overall survival rates

SARS-CoV-2 viral clearance and load as well as antibody titres.

Requirement mechanical ventilation at any time during hospital stay (yes/no)

Time until discharge from randomization.

Viral load, changes in antibody titers and cytokine profiles are analysed in an exploratory manner using paired non-parametric tests (before – after treatment).

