#### **10.5.5 Analysis of the Secondary Endpoints**

Overall survival is analyzed by using a Cox regression model adjusting for treatment and patient group, determining hazard ratios with 95% confidence intervals and (descriptive) p-values. Survival estimates are calculated using the Kaplan-Meier method together with 95% log-log-type confidence bands, and the 28-day survival rate will be given for both treatment groups together with 95% confidence intervals. Analogously as for the supplementary analysis of the primary endpoint, an IPCW model and a RPSFT model will additionally be fitted for the secondary endpoint overall survival to assess the potential treatment effect in case patients had not switched from the control to the experimental arm.

Time until discharge will be assessed similarly to the primary endpoint, providing Kaplan-Meier estimates for the cumulative discharge rate for both treatment groups and conducting a log-rank test stratified for the factor “patient group”, and censoring patients who died from any cause at day 84 in analogy to the analysis of the primary endpoint. Analogously as for the sensitivity analysis of the primary endpoint, an IPCW and a RPSFT model will additionally be fitted for the secondary endpoint ‘time until discharge’ to assess the potential treatment effect in case patients had not switched from the control to the experimental arm.

The secondary endpoint “requirement of mechanical ventilation (yes/no)” is analyzed by means of a logistic regression model adjusting for the factors treatment and patient group. Also, absolute and relative frequencies will be given for this endpoint, together with 95% confidence intervals.

The secondary endpoints SARS-CoV-2 viral load and antibody titres will be assessed over time by means of linear mixed models adjusting for treatment group, patient group, and

baseline value as fixed factors, as well as time as repeated factor using an unstructured covariance matrix, calculating least square means estimates and 95% confidence intervals.

While it is indirectly assumed by these models that data will be missing at random, i.e. that the missingness can be explained by observed covariate and outcome values, we will assess the robustness of this assumption by means of sensitivity analyses by means of pattern mixture models assuming that data will be not missing at random.

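### For cytokines the protocol fixes only a before-after test, which cannot separate a plasma effect from disease course or co-medication, although a randomised control arm is available

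*Protocol*

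**What the plan says.** Section 10.3.2 of the protocol sets the method: "Viral load, changes in antibody titers and cytokine profiles are analysed in an exploratory manner using paired non-parametric tests (before – after treatment". Section 10.5.5 then gives a second method to two of these three measures: "The secondary endpoints SARS-CoV-2 viral load and antibody titres will be assessed over time by means of linear mixed models adjusting for treatment group", with patient group, baseline value and time also in the model. Cytokines are not mentioned there. Section 10.5.6 deals only with missing data. IL-6 is also a routine local laboratory value, and the safety analysis summarises laboratory values as change from baseline, but that is not a test of the cytokine panel.

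Section 7.3.3 states what the cytokine work is for and when it is first done: "To evaluate the effects of CP onto inflammation and cytokine levels, a first analysis is performed after the first randomized 40 patients". The assay is a 48-analyte panel. A comparison group exists: "Randomisation is done either into experimental arm E or into standard arm S in a 1:1 ratio using block randomisation" (section 10.1).

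The standing of cytokines varies within the protocol. The synopsis objectives include them ("To assess SARS-CoV-2 viral clearance and load, cytokine changes over time as well as antiviral antibody titres"), and the Summary counts inflammatory cytokine changes among the secondary outcomes. Section 2.2 leaves them out ("To assess SARS-CoV-2 viral clearance and load as well as antibody titres"), as does the list of secondary outcomes in the synopsis.

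**The concern.** The question in section 7.3.3 is causal: what does plasma do to cytokines? A paired before-after test answers a different one: did the level change between two dates in the same patient? In this trial at least two other things can move cytokines between those dates. One is the disease itself; section 1.1 says the infection is associated with cytokine changes. The other is co-treatment: section 5.7 allows anti-IL6 drugs, steroids and other immune-modulating therapy and prohibits no co-medication.

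Randomisation puts the natural course and the background standard of care into both arms equally in expectation. A test that never contrasts the arms gives that up. At stake is how a secondary, exploratory result can be read: a significant before-after change in a cytokine cannot be told apart from a plasma effect, and the same applies to the look after the first 40 patients.

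**Working it through.** **Inputs**
- Plasma patients at the first look: 40 randomised at 1:1, so 40 / 2 = 20 (sections 7.3.3 and 10.1).
- Plasma patients at the end: 174 / 2 = 87 randomised, or 164 / 2 = 82 without drop-outs (section 10.3).
- Level: two-sided 5%. This is an assumption, because the protocol gives no level for the cytokine tests.
- Shared drift d, in units of the SD of the within-patient change, equal in both arms: an assumption, varied from 0 to 0.8. The protocol gives no figure.
- True plasma effect: none.

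The protocol states no figure on this point, so there is none to reproduce first.

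**Reasoning.** Write the expected change as drift + plasma effect in the experimental arm and as drift alone in the standard arm. The paired test in the experimental arm tests drift + effect = 0. The between-arm test of change tests (drift + effect) − drift = effect. With no effect, the first is false whenever there is drift and the second is true.

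Roughly, the paired statistic is centred at d × √n:
- n = 20: 0.3 × √20 = 1.34 and 0.5 × √20 = 2.24.
- n = 87: 0.3 × √87 = 2.80 and 0.5 × √87 = 4.66.

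Set against a critical value of 1.96, frequent rejection is expected.

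**Simulation.** 3,000 runs per setting with normally distributed changes. The Wilcoxon signed-rank test was applied in the plasma arm, and the Mann-Whitney test to the change between two arms of the same size. The simulation error is at most √(0.5 × 0.5 / 3000) ≈ 0.009.

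| Plasma patients | Drift d | Paired test rejects | Between-arm test rejects |
|---|---|---|---|
| 20 | 0 | 4.1% | 3.9% |
| 20 | 0.2 | 13.3% | 5.2% |
| 20 | 0.3 | 23.4% | 5.4% |
| 20 | 0.5 | 53.5% | 5.5% |
| 20 | 0.8 | 90.6% | 5.4% |
| 82 | 0.3 | 74.4% | 4.1% |
| 82 | 0.5 | 99.2% | 4.9% |
| 87 | 0.3 | 76.7% | 5.4% |
| 87 | 0.5 | 99.7% | 4.8% |

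With no drift both tests hold their level. With drift the paired test departs from it, and more so as n grows. The between-arm test stays between 3.9% and 5.5%.

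**The case against.** The strongest reply is that the protocol calls these analyses exploratory, that no decision or stopping rule hangs on the look after 40 patients, and that the synopsis words the objective as change over time, which a paired test does address. All of this stands and limits the severity. It does not remove the mismatch with section 7.3.3, which asks about the effect of plasma.

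A second reply is that the statistical analysis plan, which is not shown, may add a between-arm contrast. It may. But the protocol does not leave the method open here: it names one, and that one does not suit the stated purpose.

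Several stronger readings are tempting, and the document does not support them:
- A reader might infer that natural recovery will be reported as a plasma effect. The protocol says nothing about how the result will be reported. What can be said is that the two cannot be told apart.
- A reader might infer that only plasma recipients are tested. Section 10.3.2 does not restrict the population, and paired tests could be run in each arm. Significance in one arm and not in the other would still not be a test of the difference.
- A reader might extend the point to viral load and titres. They already have a randomised comparison in section 10.5.5. The only flaw there is that two methods stand side by side with no stated precedence.
- A reader might add multiplicity over the 48 analytes (48 × 0.05 = 2.4 expected false positives at an assumed 5% level). For an exploratory panel, how to control this is a preference that the analysis plan can settle. It is a side note and not part of the error.

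**Conclusion.** The point holds for cytokines. The one inferential method the protocol fixes cannot answer the question set in section 7.3.3, and the randomised comparison that could answer it is not specified. That conclusion follows from the structure of the test and needs no numerical assumption.

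The sizes in the table are illustrative. They rest on the assumed drift, on normal changes, on a 5% level and on no plasma effect. A smaller drift gives a smaller excess; with no drift there is none. Because the trial is open-label, co-medication after randomisation may still differ between arms. A between-arm contrast would then carry that difference as part of the consequence of assignment.

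Severity is minor to moderate: the analysis is exploratory, and neither the primary endpoint nor any confirmatory conclusion depends on it.

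**What to change.** 1. In section 10.5.5, add cytokines on the log scale to the mixed model already planned for viral load and titres. Alternatively, specify a comparison of change from baseline between randomised arms. Apply the same rule to the look after 40 patients.
2. Fix a time anchor that both arms share: the baseline sample and days since randomisation. The footnotes to Table 1 time visits from the first plasma infusion, a date that standard-arm patients lack unless they cross over. Section 6.6 lets infusion start up to 7 days after randomisation, so a study-day-3 sample in the experimental arm may fall 7 + 2 = 9 days after it.
3. Rely mainly on samples taken before crossover becomes possible at day 10. Section 7.3.3 should say which serum days go to the cytokine panel; it lists day 3 both as scheduled and as optional.
4. In section 10.3.2, keep the paired tests as descriptive only, and state that the section 10.5.5 model governs viral load and titres.
5. Align the Summary, the synopsis, section 2.2 and section 10.3.2 on whether cytokines are a secondary objective.

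The cost is mostly wording, plus agreement on the time anchor. Section 7.3.3 does not restrict serum collection by arm, so no new sampling appears necessary. The between-arm contrast is less powerful than a before-after test: with equal arms the variance of the difference is σ²/n + σ²/n = 2σ²/n, so its standard error is √2 ≈ 1.41 times that of a single-arm mean change. That is the price of isolating the plasma effect.

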### 10.2.3 Safety Endpoints

This includes all AEs, their severity, SAEs, the relation of AEs to the study treatment, dose modifications for toxicity and discontinuation of study treatment during the trial phase. Toxic effects are graded according to the National Cancer Institute Common Toxicity Criteria (CTCAE) version 5.0.

## 10.3 Sample Size Calculation

Based on recently published data median time to an improvement defined as two points on a seven point ordinal scale or live discharge from the hospital is assumed to be at day 16 from randomization. This median estimate considers patients who died without an improvement as censored at day 84 (right-censoring), which ensures that those patients are considered as “not improved” over the whole observation period. In our trial, we follow the same analysis strategy as in Cao *et al.*, 2020 who also censored deceased patients at the end of follow-up.

We assume that based on the mechanism of action (neutralizing antibodies) a rapid improvement is induced by fresh frozen plasma from subjects after convalescence of SARS-CoV-2 infection on two days from two different donors with a median time of 10 days (HR=1.6). Assuming exponentially distributed event times, these assumptions correspond to a hazard of  $\lambda_C = 0.043$  for the control arm, while the corresponding hazard in the experimental arm should amount to  $\lambda_E = 0.043 \cdot 1.6 = 0.69$ .

While it is allowed for patients from the control arm to switch to the experimental arm starting at day 10 (see section 6.8), we assume this will not have a major effect on the median time of clinical improvement for these patients, since we expect that plasma infusions will have a larger advantage if given early. While methods for handling patients switching from control to treatment group are available, they are subject to strong and unverifiable assumptions. Hence, we will ignore treatment switch in the primary analysis, representing a treatment policy strategy (see Section 10.2.1), which can be regarded as a conservative approach since switching is only allowed from the control to the experimental arm. However, in supplementary analyses of the primary endpoint, we will consider such a hypothetical scenario in which a treatment effect is estimated for the case that patients would not have switched by means of inverse probability censoring weighting according to Robins & Finkelstein, relying on the assumption that there are no unmeasured confounders influencing the probability to switch, and a rank preserving structural failure time (RPSFT) model, assuming a common treatment effect which remains constant over time, regardless when treatment is initiated.

Since patients might die before experiencing a clinical improvement or being discharged from the hospital, death will be taken into account via censoring deceased patients at last day of follow-up (day 84). Based on recently published data, the mortality rate is assumed to be about 20% in the control arm. Thus, we expect that the cumulative improvement rate of the control group will not become larger than 0.8. Hence, fewer improvement events are expected during the follow-up of 84 days than under the assumption of an exponential distribution, since the improvement curves will flatten at some point. In case of the control group, the flattening is expected to occur at day 38, since the assumed cumulative improvement rate at day 38 amounts to  $\exp(-\lambda_C \cdot 38) = \exp(-0.043 \cdot 38) \approx 0.8$ . Accordingly, we conservatively assume a follow-up length of 38 days for the sample size calculation to properly estimate the probability of experiencing the event of interest, even though the actual follow-up for each patient will be longer.

To detect the assumed difference between treatment groups using a log-rank test comparing the cumulative improvement curves for the primary endpoint using a significance level of 5% (two-sided) with a power of 80%, a total number of 174 patients is required for the entire trial (87 patients per group) when additionally considering a dropout rate of 5%, meaning that n=164 patients who do not prematurely drop out of the study are required to be enrolled. The required number of events which was calculated using the formula by Schoenfeld, amounts to 142. It is expected that adjusting for the covariate “patient group” in the analysis will lead to an increase in power. Sample size calculation was done conservatively assuming an equally long follow-up period of 38 days for every patient. Sample size calculation was done using RPACT v 2.0.6.

For the sample size calculation, it was assumed that there would be a consistent median time to improvement and overall survival rate across all 4 patient groups. Since this might not necessarily be the case, and it could be likely that patients in group 1 and 2 might have a shorter median time to improvement, we conducted a simulation study to explore the robustness of our model under varying assumptions for the median event times. For our simulation study, we assumed exponentially distributed event times, with a median time to improvement of 16 days across all patient groups in the control group ( $\text{med}_C^1 = \text{med}_C^2 = \text{med}_C^3 = \text{med}_C^4 = 16$ ), while we assumed differing median times to improvement in the patient groups 1 & 2 compared to patient groups 3 & 4 ( $\text{med}_E^1 = \text{med}_E^2$ ,  $\text{med}_E^3 = \text{med}_E^4$ ) in the experimental group. We considered a sample size of n=164 evaluable patients for the whole

trial, with 42 patients belonging to groups 1 and 3 each, and 40 patients belonging to groups 2 and 4 each corresponding to patient group membership probability of about 25% for all four groups. Also, we assumed a 38-day mortality rate of 20% in the control arm, while we assumed that the corresponding mortality rate in the experimental arm amounted to 13% (corresponding to a HR for overall survival of 1.6) across all four patient strata assuming exponentially distributed survival times. We simulated 10,000 trials per scenario corresponding to a maximum standard error of  $\sqrt{0.5 \cdot 0.5 / 10000} = 0.005$  for the simulated power.

We used a stratified log-rank test to assess whether the cumulative improvement curves in the two treatment groups (experimental/control) would be equal at a two-sided significance level of  $\alpha=0.05$  stratifying for the factor “patient group” for analysis. The analysis of the simulated datasets was done using the PROC LIFETEST procedure in SAS v9.4. The results are shown in Table 3.

**Table 3: Power for the RECOVER trial considering varying treatment effects across patient groups, assuming medC1= medC2 = medC3 = medC4=16 days**

| Median time to improvement in intervention group for patient groups 1 and 2 in days | Median time to improvement in intervention group for patient groups 1 and 2 in days | Simulated Power 1- $\beta$ |
|-------------------------------------------------------------------------------------|-------------------------------------------------------------------------------------|----------------------------|
| med E  = med E  =10                   | med E  = med E  =10                   | 0.785                      |
| med E  = med E  =9                    | med E  = med E  =11                   | 0.794                      |
| med E  = med E  =8                    | med E  = med E  =12                   | 0.813                      |

*Assumptions:  $\alpha=0.05$  (two-sided), 10,000 simulations per scenario, n=164 patients not prematurely dropping out of the trial enrolled.*

The results in Table 3 show that the aspired power of 80% is approximately achieved in all scenarios, with an even increased power in case of a treatment effect differing between patient groups in the experimental group. This indicates that our planned analysis strategy will achieve the aspired power even under varying treatment effects across the patient strata, when the “average” median time to improvement in the experimental group still amounts to 10 days.

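### Table 3's rise in power comes from a larger average hazard ratio, not from effects that differ between patient groups

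*Protocol*

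**What the plan says.** Section 10.3 sizes the trial "using a significance level of 5% (two-sided) with a power of 80"%, with a control median of 16 days and the experimental arm "with a median time of 10 days (HR=1.6"). This gives 142 events and 164 evaluable patients, or 174 with 5% dropout.

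A simulation then explores robustness to effects that vary by patient group. It has 164 patients in groups of 42, 40, 42 and 40, "corresponding to patient group membership probability of about 25% for all four groups", "with a median time to improvement of 16 days across all patient groups in the control group", and 38-day mortality of 20% (control) and 13% (experimental). The test is the log-rank test stratified by patient group.

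Table 3 gives power of 0.785, 0.794 and 0.813 for experimental medians of 10/10, 9/11 and 8/12 days. The second column is labelled groups 1 and 2 again (for example "med E 1 = med E 2 =11"). The text of 10.3 makes clear that groups 3 and 4 are meant, and it is read so here.

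The text concludes that about 80% is reached throughout, "with an even increased power in case of a treatment effect differing between patient groups in the experimental group". It attaches a proviso: the average experimental median must stay at 10 days. Before the simulation, 10.3 also states the expectation that adjusting for patient group "in the analysis will lead to an increase in power".

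**The concern.** Under proportional hazards within strata, the power of a stratified log-rank test is driven by the event-weighted average of the stratum log hazard ratios. With exponential times, each of these is the log of a ratio of medians, and the logarithm is concave. Moving two medians apart while fixing their arithmetic mean therefore lowers their geometric mean and raises the average log hazard ratio. Rows 2 and 3 assume a stronger treatment on average than row 1, so they cannot show what heterogeneity alone does.

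At stake is a favourable design property that readers will take from the protocol: that unequal effects between risk groups are harmless or even helpful. The simulation does not show this.

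**Working it through.** **Inputs (all section 10.3).** Two-sided alpha 0.05; control median 16 days in every group; experimental medians 10/10, 9/11, 8/12; 164 patients in groups of 42/40/42/40, so groups 1+2 hold 82 of 164; 38-day mortality 20% and 13%; 10,000 simulated trials per row. The horizon of the Table 3 simulation is not stated, so 38 days (used for the sample size) and 84 days (actual follow-up) were both run.

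**1. The planned size reproduces.** Events = 4(1.960 + 0.842)² / (ln 1.6)² = 142.1. With event probabilities of 0.807 and 0.928 by day 38 (mean 0.868), N = 142.1 / 0.868 = 163.8, against the stated 164.

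**2. The average effect in each row.** With two halves of equal size, mean log HR = [ln(16/a) + ln(16/b)] / 2.

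| Medians a/b | Arithmetic mean | Mean log HR | Average HR | Geometric mean median |
|---|---|---|---|---|
| 10/10 | 10 | 0.4700 | 1.600 | 10.00 |
| 9/11 | 10 | (0.5754 + 0.3747)/2 = 0.4750 | 1.608 | 9.95 |
| 8/12 | 10 | (0.6931 + 0.2877)/2 = 0.4904 | 1.633 | 9.80 |

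**3. Is that enough to explain the table?** Take power ≈ Φ(√d × mean log HR / 2 − 1.960) with d = 142, so √142 / 2 = 5.958:
- 10/10: Φ(2.800 − 1.960) = 0.800
- 9/11: Φ(2.830 − 1.960) = 0.808
- 8/12: Φ(2.922 − 1.960) = 0.832

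The predicted gains are 0.8 and 3.2 points. The printed gains are 0.9 and 2.8.

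**4. Simulation.** Stratified log-rank test, exponential times, deaths kept in the risk set to the end of follow-up, 80,000 trials per cell.

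| Scenario | 38 days | 84 days |
|---|---|---|
| Table 3 rows: 10/10, 9/11, 8/12 (printed 0.785, 0.794, 0.813) | 0.792, 0.799, 0.819 | 0.782, 0.790, 0.807 |
| Homogeneous, same average log HR as 9/11 and 8/12: medians 9.95 and 9.80 | 0.800, 0.820 | 0.790, 0.813 |
| Average log HR fixed at ln 1.6: 10/10, 9/11.1, 8/12.5 | 0.793, 0.789, 0.787 | 0.787, 0.782, 0.781 |

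The printed values reproduce within about one point. A homogeneous effect of the same average size gives essentially the same power as the heterogeneous row. With the average fixed, the gain is gone. Run-to-run noise is up to about half a point, as the repeated 10/10 cells show; further runs of the fixed-average rows fell between 0.775 and 0.793. If the average hazard is fixed instead (9/11.25, 8/13.33), power falls to 0.782 and 0.737 at 38 days. The direction of the apparent heterogeneity effect thus depends on which average is held constant.

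**5. Joint share of groups 1+2, medians 8/12.** The shares other than one half are assumptions; the protocol gives no alternative split.

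| Groups 1+2, share of 164 | 38 days | 84 days |
|---|---|---|
| 29% | 0.669 | 0.678 |
| 39% | 0.753 | 0.744 |
| 49% | 0.810 | 0.801 |
| 56% | 0.854 | 0.836 |
| 61% | 0.877 | 0.864 |

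At about 35% (58 patients) power is roughly 0.71-0.72, and at about 26% (42 patients) roughly 0.64-0.66. The split inside each pair does not matter: 70/12/12/70 gives 0.796 for 9/11 and 0.819 for 8/12 at 38 days.

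**6. Adjustment for patient group.** With HR 1.6 in every group, 38 days, and control medians that differ by group (assumed 12/12/20/20, 10/14/19/24, 8/12/20/30), the stratified test has power 0.783, 0.784 and 0.775. The unstratified test has 0.773, 0.753 and 0.675.

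**The case against.** The strongest reply is that nothing printed is miscalculated. The three powers reproduce, the averaging rule is disclosed with a proviso, power is described only as approximately 80%, and Table 3 sets neither N nor the test. All of that stands. It does not rescue the inference, because the proviso about the average median is itself what makes the average hazard ratio rise.

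Three stronger readings are tempting, and the protocol does not support them.
- *That the result needs exactly 25% in each group.* The protocol says about 25% and simulates 42/40/42/40. Only the joint share of groups 1+2 matters, and a share above half raises power.
- *That power is really 65-72%.* Those values need assumed shares of about 26-35%. Such shares also reduce the average effect: with 58 of 164 patients in groups 1+2, the mean log HR is (58 × 0.6931 + 106 × 0.2877)/164 = 0.431 (HR 1.54), and the average median is (58 × 8 + 106 × 12)/164 = 10.6 days. They lie outside the protocol's proviso, so they show sensitivity to case mix and do not contradict its text.
- *That the sentence on adjustment is wrong.* Read as a comparison with an unstratified test, it is supported by step 6. Table 3's base row cannot test it, since all control medians there are 16 days.

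**Conclusion.** The statement that differing effects increase power is wrong as written. The rise of 2.8 points (0.785 to 0.813) is fully explained by an average hazard ratio that grows from 1.600 to 1.633. At a fixed average log hazard ratio of ln 1.6, power is flat to slightly lower, about 0.77-0.80 across both horizons. This rests on the protocol's own exponential, mortality and group-size assumptions, with deaths kept at risk as in its primary analysis.

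Two qualifications belong with it. The table depends on groups 1+2 making up about half of the patients. The protocol expects this, but randomisation stratified by group balances the arms and does not control group shares, and no quota was found. And adjustment for patient group is no reserve above 80%: the base row already uses the stratified test and prints 0.785, which is (0.800 − 0.785)/0.0041 = 3.7 standard errors below 0.80, where 0.0041 = √(0.785 × 0.215/10,000).

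The practical size is modest. The planned 174 patients rest on the homogeneous HR of 1.6 and are not put in question by this point.

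**What to change.** - Rerun Table 3 with the average log hazard ratio fixed at ln 1.6 (10/10, 9/11.1, 8/12.5), stating the simulation horizon and how deaths were coded, and correct the second column label.
- Replace the conclusion on increased power with: heterogeneity between patient groups does not itself raise power; at an average hazard ratio of 1.6 the planned stratified test has about 78-79% power in the base scenario.
- Keep the sentence on adjustment, but say that the gain is relative to an unstratified test when groups differ in prognosis, and is not a margin above 80%.
- Optionally, add rows with the joint share of groups 1+2 below and above half, labelled as assumptions.

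The cost is one rerun of an existing simulation and a reworded paragraph. The stated power becomes slightly less favourable; the number of patients and the primary analysis stay as they are.
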